### Outcome measures

3.9

The primary efficacy endpoint will be NRS at baseline, after the 1st treatment, after the final treatment and 4 weeks after the final treatment. The NRS is a segmented numeric version of the visual analog scale (VAS) in which a respondent selects a whole number (0–10 integers) that best reflects the intensity of pain. Thus, we select NRS as the primary measurement to assess the improvement of pain.

Secondary measurements will be as follows:

Fugl–Meyer score: The FMA score consists of 17 items, ranging from 0 to 34, with lower scores demonstrating poorer movement function. In our trial, we just assessed the upper extremity Fugl–Meyer which includes 10 items and ranging from 0 to 20 at baseline, after the final treatment and 4 weeks after the final treatment.

Constant score: A supplementary assessment of function of the shoulder joint will be assessed by the constant score scale at baseline, after the final treatment and 4 weeks after the final treatment.

Short-form of McGill pain questionnaire (MPQ-SF) score: The MPQ-SF is a multidescriptive measure of pain that consists of 22 pain questions. It reveals the nature of shoulder pain. It will be evaluated at baseline, after the final treatment and 4 weeks after the final treatment.

Quality of life (QOL) score: QOL will be evaluated using the Chinese version of EQ-5D-5L^[25]^ at baseline, after the final treatment and 4 weeks after the final treatment.

ROM: Pain-free passive range of motion (PROM) of the shoulder was designated as the ROM attained in the most painful position and was measured using a digital goniometer in 6 directions: flexion, extension, abduction, adduction, external rotation, and internal rotation. Five directions of the shoulder joint were measured (flexion, abduction, adduction, internal rotation, and external rotation), while participants were lying in a supine position. In addition, shoulder extension was measured in the side-lying position. PROM was also evaluated at baseline, after the final treatment and 4 weeks after the final treatment.

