### Sample size calculation

3.12

The trial is designed to determine the role of FSN for treating HSP among stroke survivors. Therefore, NRS change will be used as an evaluation index. According to our previous pilot study, the change of NRS before and after treatment in the treatment group was shown to be 3.40 ± 0.48 (n = 10) and that in control group was 3.10 ± 0.23 (n = 10). Sample size was estimated using the following formula: 

where n represents the number of samples required, n = n_1_ + n_2_, *Q*_1_ = n_1_/n, *Q*_2_ = n_2_/n with a significance level (*α* = 0.05) of a 2-sided 2-sample *t* test and 80% power to detect a difference between the 2 groups. Thus, a total sample size of 60 patients will be recruited allowing for 10% of attrition, with 30 in each.

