### Statistical analysis

3.13

The SPSS 20.0 (IBM SPSS Statistics, IBM Corp, Somers, NY) will be used to analyze the data. Quantitative data will be presented as mean ± standard deviation. NRS, Fugl–Meyer, Constant, MPQ-SF, QOL, and ROM scores will be conducted between the 2 groups by a superiority independent sample *t* test with a 95% confidence interval. The incidence of complications and adverse events will be compared by Chi-squared test. Any missing data will be replaced by the last measured value. For all analyses, *P* values of <.05 will be considered statistically significant.

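### Carrying the last value forward scores treatment-phase dropouts at or near baseline, which at the planned 10% attrition can undo the plan's own power and biases the estimate if dropout differs by arm

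*Protocol article*

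**What the plan says.** Protocol article, 3.13 Statistical analysis: "Any missing data will be replaced by the last measured value". The sentence is unconditional and applies to every outcome. The article states no other missing-data method and no sensitivity analysis. The groups are to be compared by an independent-sample t test.

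Protocol article, 3.9 Outcome measures: "The primary efficacy endpoint will be NRS at baseline, after the 1st treatment, after the final treatment and 4 weeks after the final treatment". Fugl–Meyer, Constant, MPQ-SF, EQ-5D-5L and range of motion are taken only at baseline, at end of treatment and four weeks later.

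Protocol article, 3.12 Sample size calculation: "the change of NRS before and after treatment in the treatment group was shown to be 3.40 ± 0.48 (n = 10"). For usual care the pilot gave a mean change of 3.10 with SD 0.23, also from 10 patients. The recruitment target derived from these figures is stated as follows: "a total sample size of 60 patients will be recruited allowing for 10% of attrition, with 30 in each".

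**The concern.** Both arms are expected to improve by more than 3 points, and the effect being sought is the 0.30-point gap between them. NRS has no visit between session 1 and week 4, a span that holds 19 of the 20 FSN sessions. For a patient lost in that span, the rule supplies a value from before nearly all of the treatment and the t test treats it as an observed end-of-treatment score. For the secondary scores the value supplied is always baseline, so the imputed change is exactly zero.

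Two things are at stake. Imputed changes far below the completers' changes inflate the SD, so power is lost even when dropout is equal in the two arms. If dropout is unequal, the arm means are pulled down by different amounts and the treatment estimate is biased.

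**Working it through.** **Inputs.** Mean changes 3.40 and 3.10, SDs 0.48 and 0.23, two-sided α 0.05, 80% power, 30 per arm and 10% attrition, all from 3.12. The variable analysed is taken to be NRS change at end of treatment, as in 3.12. The carried change c is not given in the protocol, so it is varied.

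**The plan's own figure.** Pooled SD = √((0.48² + 0.23²)/2) = √0.14165 = 0.376. The normal approximation gives n = 2 × (1.960 + 0.842)² × 0.14165 / 0.30² ≈ 24.7, so 25 per arm; the exact t calculation gives 26 (power 80.5%). With attrition, 26/0.9 = 28.9, so 29 per arm or 58 in total, against 60 stated. The sample size is in effect reproduced and is not in dispute. Power is 86% with 30 per arm, and 82% with 27 completers per arm if missingness is unrelated to outcome.

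**Equal dropout under the stated rule.** Let each patient be lost during treatment with probability 0.10 and be given a fraction f of the arm's mean change. For the FSN arm at f = 0:

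- Mean = 0.9 × 3.40 = 3.06. The control mean is 0.9 × 3.10 = 2.79, so the difference is 0.27.
- SD = √(0.9 × 0.48² + 0.9 × 0.1 × 3.40²) = √(0.207 + 1.040) = 1.12, against 0.48 planned.

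Simulated power of the pooled t test, 30 per arm:

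| Carried fraction of expected change | Mean difference | Power |
|---|---|---|
| No dropout | 0.30 | 86% |
| 0% | 0.27 | 19% |
| 50% | 0.285 | 44% |
| 75% | 0.29 | 73% |

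These are averages over random dropout counts. With exactly 3 dropouts in each arm and c = 0, power is about 0.1%; at c = 1 it is about 7% and at c = 2 about 50%.

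**Unequal dropout, true difference 0.30.** With 3 FSN dropouts and no control dropouts:

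- c = 0: FSN mean = 27 × 3.40 / 30 = 3.06; difference = 3.06 − 3.10 = −0.04.
- 50% carried (c = 1.70): FSN mean = (27 × 3.40 + 3 × 1.70) / 30 = 3.23; difference = +0.13.

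The excess number of dropouts that moves the estimate by the whole 0.30 is 0.30 × 30 / (μ − c). For FSN (μ = 3.40) this is 2.6, 3.8 and 6.4 at c = 0, 1 and 2. For control (μ = 3.10) it is 2.9, 4.3 and 8.2.

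**Unequal dropout, no true difference.** Both arms have mean 3.10 and SD 0.376, with an assumed 5% against 15% random dropout. The two-sided type I error is about 21% with zero change carried and about 16% with half carried. Nearly all rejections favour the arm with less dropout. With 10% in both arms it stays at about 5%.

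**The case against.** Several stronger readings are tempting, and the protocol does not support them.

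- **Every dropout is treated as barely improved.** This holds only for losses during treatment. A patient lost in follow-up carries the week-4 value, which assumes the effect is maintained. For NRS the first-session value may already show relief: the Introduction says FSN can relieve pain rapidly. The carried change is therefore uncertain for NRS, though not for the secondary scores.
- **Adding 10% for attrition contradicts imputing the dropouts.** It does not. Recruiting extra patients can compensate for lost information even when dropouts stay in the analysis.
- **Dropout will differ by arm.** Participants are unblinded (3.4) and only one arm has the added needling, so imbalance is possible. But no arm-specific rate is given, and recruitment is mainly of inpatients, which favours retention. Section 3.10 stops FSN after a severe event; it does not say that outcome assessment stops.
- **A few unequal dropouts create a significant effect.** A shifted estimate is not the same as a significant one, because carried values also inflate the SD. Under the null with c = 0, a 2 v 4 split (FSN v control) shifts the difference by 0.21 yet produces almost no false positives; 0 v 3 gives 19% in favour of FSN. Bias as large as the 0.30 target needs marked imbalance together with near-zero carried change.

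It is also fair to say that the steep loss of power reflects the very small pilot SDs, from 10 patients per arm. With a larger true SD, carried values would add proportionally less. What stands is that the rule is fixed in the text, suits this visit schedule poorly, and does damage on the plan's own figures even when dropout is equal.

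**Conclusion.** The concern holds for patients lost during the treatment phase. At the planned 10% attrition, equal and random in both arms, the stated rule lowers power from 86% to about 19% (no change carried), 44% (half) or 73% (three quarters), against about 82% from 27 completers per arm if missingness is unrelated to outcome. Equal dropout only dilutes the NRS estimate, from 0.30 to 0.27 at most, and leaves type I error at 5%. Unequal dropout biases the estimate in either direction: three extra FSN losses turn +0.30 into −0.04 with zero change carried, or +0.13 with half carried.

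The direction of these effects follows from the rule and the visit schedule. Their size rests on the pilot means and SDs, on all attrition falling within treatment, and on assumed values for the carried fraction and for the 5% v 15% split, none of which the protocol gives. Because the rule governs the primary result and the correction is cheap, it should be changed before any outcome data are analysed.

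**What to change.** Replace the missing-data sentence in 3.13 with the following.

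1. **NRS.** Analyse change from baseline at all post-baseline visits by randomised group, using all observed values, in a mixed model for repeated measures (SPSS MIXED) with treatment, visit, treatment-by-visit interaction and baseline NRS.
2. **Secondary scores.** Use the same model at end of treatment and four weeks later, or baseline-adjusted ANCOVA on observed values. With no visit between baseline and end of treatment, the model gains little over ANCOVA here.
3. **Data collection.** State that scheduled outcome assessments continue after a participant stops treatment.
4. **Sensitivity analyses.** Keep last value carried forward only in this role, next to an analysis in which FSN dropouts are assumed to behave like usual care.

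The cost is mainly analysis wording, with a method available in the software already named, plus the effort of assessing patients who have stopped treatment. Treatment and sample size do not change. The drawback is that the model assumes data are missing at random, which cannot be tested and which, for a treatment-phase dropout, rests on at most one post-baseline NRS value. The sensitivity analyses are there to examine that assumption.

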### Quality control

3.14

Before the trial, all the acupuncturists, nurses, and assessors will be trained strictly to guarantee homogeneity in the measurement data and ensure high-quality data results. The training content will include study protocol, diagnosis, inclusion, and exclusion criteria, recording method of CRF, FSN techniques, disposal of bleeding. All the study data will be recorded on the case report form. Dropouts and withdrawals from the study will be recorded in detail based on the intervention and follow-up periods. Data will be uploaded and verified by other 2 researchers who were not involved in the trial. This trial will be monitored by the Scientific Research Department of GuangDong Second Hospital of Traditional Chinese Medicine every 1 week.

### Ethics and dissemination

3.15

We strictly follow the principles of the medical ethics of the Declaration of Helsinki^[26]^ with the approval of the Ethics and Research Committee of GuangDong Second Hospital of Traditional Chinese Medicine, China. If there are any protocol modifications, we will report to the Ethics and Research Committee for approval. All patients will be recruited from the Department of Acupuncture and Rehabilitation, GuangDong Second Hospital of Traditional Chinese Medicine. Informed consent will be obtained from all study participants. Participant information will be protected. All experimental data will be stored in a secure storage area with access limited to the researchers alone. We will disseminate the results of this study in meetings or publications when the trial is completed.

### Patient and public involvement

3.16

This trial was designed to evaluate the add-on effects of FSN for HSP. In clinical practice, conventional acupuncture was widely used to treat complications of stroke, including HSP; however, the effect was always slow and not convinced for all patients. FSN may increase the effectiveness, hence significantly relieve pain and improve patients’ quality of life. The outcome measures used in this study were commonly used in clinical trials of HSP, and considered as important endpoints in our treatment. Patients with HSP after stroke in our clinical department were consulted prior to the trial design; in particular, the treatment frequency and duration of this trial were summarized from our clinical experience and patients’ feedback. The recruitment of patients will be carried out in our clinical department. However, those who were involved in the consultation related to the trial design will not be included as trial participants. Upon the completion of this trial, we will present the trial results in a peer-reviewed journal, or presented at international conferences. Once this manuscript is published, a brief summary of results using plain language will be sent to all trial participants. The burden of intervention will not be assessed by trial participants.

## Discussion

4

This trial was designed to evaluate the effects and safety of FSN combined conventional acupuncture for the treatment of HSP. Evaluation of NRS, Fugl–Meyer, constant, MPQ-SF, QOL, ROM scores, as well as adverse events will be recorded and reported in a 4-week treatment and 4-week follow-up period. Moreover, this trial also involves incorporate appropriate allocation concealment and blinding of outcome assessors, data manager, statistics analyzer and will be reported in accordance with CONSORT 2010 and STRICTA 2010.^[21,22]^

Acupuncture has been practiced for more than 2500 years in China as an important therapeutic technique of traditional Chinese medicine. The effect of conventional acupuncture for HSP had been evaluated by several systematic reviews^[17,27,28]^; however, controversial conclusions were reached, which suggested that the effect of conventional acupuncture alone for HSP may be limited. FSN was invented by a acupuncturist in China named Fu-Zhonghua, and has been widely used in many clinical treatments.^[29–31]^ The needle-insertion layers of FSN is subcutaneous fascia, which has been a new research focus in recent years and considered to be closed related with pathologic mechanism of majority of diseases.^[32–34]^ According to FSN theory, the insertion points can be anywhere on the skin surrounding the painful spot and the distance between insertion point and pain spot is not fixed. In our trials, insertion points will be located 7 to 8 cm above or inferior to the pain spot to make the intervention repeatable. Moreover, patients should not feel numbness or aching during FSN intervention, which is similar to the characteristic of wrist-ankle acupuncture therapy.^[35]^ A recent study conducted by Jin et al^[36]^ had concluded that FSN combined with constraint-induced movement therapy could effectively improve spasticity and arm function in patients with stroke and spastic hemiparesis despite that it is just a case report. So we design this study to systematically observed the effect of FSN for HSP, to investigate if FSN could strengthen the clinical effect of UC treatment alone.

In our trial, strict quality control procedures have been applied to avoid bias, such as randomization and allocation concealment, assessor blinding and adequate sample size. However, methodologic limitations still exist. First, the trial is conducted in a single center. Thus, regional differences cannot be distinguished. Second, all the participants may have a higher expectation of acupuncture therapy because the trial was carried out in hospital of traditional Chinese medicine. Third, the therapists and the participants cannot be blinded in this study due to wide differences between FSN and UC treatment.

### Trial status

4.1

This is protocol version 1.0, version date is November 11, 2018. Participants are not being recruited. Recruitment will begin on June 1, 2019. The trial is planned to be completed by December 31, 2020.
